### **Closed UK sites**

There are limitations of registry data collection, in that seriousness and relatedness cannot be assessed by this method of data collection once the sites have closed. A risk adapted approach is now merited as the safety profile of anastrozole is well-established across multiple trials and long follow up periods (as of 31 July 2016, the total cumulative exposure

figure for Arimidex (anastrozole) in the marketed setting is calculated to be in excess of 8 million patient years). Anastrozole has also been recommended by the National Institute of Clinical Excellence (CG164) as a first-line therapy for women at risk of breast cancer without osteoporosis. All participants are now off-treatment and the half-lives of anastrozole is relatively short (50 hours), therefore collection of follow up data from the digital registries poses a minimal risk to participants.

All data received via registries in the UK will be assessed by the data management (DM) team as part of a bulk dataset. This long-term follow-up data will be received by an independent data manager on a yearly basis from the various devolved UK data registries and Public Health England as previously described. The data will be screened for deaths, new and recurrent breast cancers and other ICD-coded events listed in Table 1. All newly identified events that meet the criteria listed in 4.5.1.2 will be sent to AZ as an 'unverified' line listing once a year. This will provide data on AEs that should be reported in the long term follow up period under expedited conditions but with the limitations discussed above.

#### **4.5.4.4 Suspected Unexpected Serious Adverse Reaction (SUSAR) and Serious, Suspected Adverse Reactions (SSARs)**

Local centre investigators are responsible for assessing seriousness and relatedness of an adverse reaction.

It will be the responsibility of AstraZeneca to confirm whether any reported SARs are a Suspected Unexpected Serious Adverse Reaction (SUSAR) or a Serious Suspected Adverse Reaction (SSAR). AstraZeneca will forward any SUSARs to the regulatory authority. (Appendix 3a and 3b)

#### **SUSARs identified from UK registry data post UK site closures**

It will be noted in the DSUR report that seriousness and relatedness cannot be determined from the digital registries.

If a SUSAR is identified by AZ from the registry data, then this will be reported as such. However, the usual timelines for reporting a SUSAR cannot be adhered to with registry data events.

See Appendix 3a and 3b for a summary of safety reporting procedures

## **5. Toxicity and Hazards**

Anastrozole has been used in the treatment of breast cancer since 1995 and is generally well tolerated. Reported adverse events have usually been mild to moderate with only a few withdrawals from treatment due to undesirable events. These include hot flushes, vaginal dryness and hair thinning. Anastrozole may also be associated with gastrointestinal disturbances (anorexia, nausea, vomiting and diarrhoea), asthenia, arthralgia, somnolence, headache or rash.

Anastrozole has been used in advanced breast cancer and has been found to be at least as effective as tamoxifen, but with fewer side effects (Bonnetterre *et al.*, 2000) (see Table 5). Until recently its use as an adjuvant in early breast cancer has been restricted to clinical trials, but it has now been licensed for use in the adjuvant setting in several countries.

As all women will be postmenopausal, pregnancy risk will not be an issue in this trial.

Results from an adjuvant trial (ATAC) (ATAC Trialists, 2002) enrolling over 9000 postmenopausal patients indicate that anastrozole is more effective in reducing early recurrences than tamoxifen ( $P=0.013$ ). At the time of this report, the median follow-up was 33.3 months and median duration of treatment was 30.7 months. The side effect profile is also generally more favourable (Table 5), with fewer endometrial cancers, thromboembolic events, strokes, and hot flushes. However, musculoskeletal symptoms (mostly arthralgia) and fractures of osteoporotic sites and other sites are increased. It is not yet clear the extent to which bone loss associated with anastrozole. Also no studies to date have been conducted to investigate concomitant use of vitamin D and calcium or bisphosphonate in

combination with anastrozole. Because of the profound reduction of circulating oestrogen levels in women taking anastrozole, effective management of potential bone loss is likely to be important. Detailed bone density studies are currently underway in the adjuvant trials, and further studies will also be undertaken within this trial. A separate bone sub-study will address these issues in the prevention stratum.

**Table 5. Pre-specified adverse events in the ATAC adjuvant trial (%)**

|                                   | Anastrozole
(N=3125) | Tamoxifen
(N=3116) | Combination
(N=3125) |
|-----------------------------------|-------------------------|-----------------------|-------------------------|
| Hot flushes                       | 34.3                    | 39.7                  | 40.2                    |
| Nausea and vomiting               | 10.5                    | 10.2                  | 11.7                    |
| Fatigue/Tiredness (Asthenia)      | 15.7                    | 15.1                  | 14.0                    |
| Mood disturbances                 | 15.5                    | 15.2                  | 15.6                    |
| Musculo-skeletal disorders        | 27.8                    | 21.2                  | 22.1                    |
| Vaginal bleeding                  | 4.5                     | 8.1                   | 7.7                     |
| Vaginal discharge                 | 2.8                     | 11.4                  | 11.4                    |
| Endometrial cancer    | 0.1                     | 0.5                   | 0.2                     |
| Fractures                         | 5.8                     | 3.7                   | 4.6                     |
| Fractures of spine/hip/wrist      | 2.2                     | 1.4                   | 1.6                     |
| Ischaemic cardiovascular disease  | 2.5                     | 1.9                   | 2.2                     |
| Ischaemic cerebrovascular event   | 1.0                     | 2.1                   | 1.6                     |
| Venous thromboembolic events      | 2.1                     | 3.5                   | 4.0                     |
| Deep venous thromboembolic events | 1.0                     | 1.7                   | 2.0                     |
| Cataracts                         | 3.5                     | 3.8                   | 3.4                     |

 Excluding patients with hysterectomy at baseline

Anastrozole is not recommended for use in premenopausal women as safety and efficacy have not been established in this group of women. Anastrozole has not been investigated in patients with severe hepatic or severe renal impairment, but women with these conditions

will not be eligible for the trial. The potential risk/benefit to such patients should be carefully considered before administration of anastrozole.

Antipyrine, warfarin and cimetidine clinical interaction studies indicate that the co-administration of anastrozole with other drugs is unlikely to result in clinically significant drug interactions mediated by cytochrome P450.

Hepatic changes (elevated gamma-GT or less commonly alkaline phosphatase) have been reported in patients with advanced breast cancer, many of whom had liver and/or bone metastases. A causal relationship for these changes has not been established. Slight increases in total cholesterol have also been observed in clinical trials with anastrozole.

Daily doses of anastrozole up to 10 mg do not have any effect on cortisol or aldosterone secretion, measured before or after standard ACTH challenge testing. Corticoid supplements are therefore not needed.

Events of Carpal Tunnel Syndrome have been reported in patients receiving anastrozole treatment in clinical trials in greater numbers than those receiving treatment with tamoxifen. However, the majority of these events occurred in patients with identifiable risk factors for the development of the condition.

In the ATAC trial, ischaemic cardiovascular events were reported more frequently in patients treated with anastrozole compared to those treated with tamoxifen, although the difference was not statistically significant. The observed difference was mainly due to more reports of angina pectoris and was associated with a sub-group of patients with pre-existing ischaemic heart disease.

Sensory disturbances (including paraesthesia, taste loss and taste perversion) have been reported more frequently in patients receiving anastrozole than those on tamoxifen in clinical trials. In order to ensure that participants still on treatment are aware of this

newly listed side effect (added to Arimidex Summary of Product Characteristics [SmPC] v160114), they must be informed of this at their next clinic appointment.

The full list of adverse reactions to anastrozole is available as a separate document. (Astra Zeneca Core Data sheet)

## **6. Analysis of Data and Statistical Considerations**

### **6.1 Randomisation**

Analysis will be based on randomised treatment option (intent to treat or ITT). For this reason, it is important to attempt to ensure good compliance before randomisation.

Randomisation will be stratified by individual major (hub) centre only. The randomisation will not be stratified for the other risk factors, but they will be used to achieve retrospective stratification at the time of analysis.

### **6.2 Endpoints**

The primary endpoint is the development of locally histologically confirmed breast cancer, both invasive and non-invasive (i.e. including DCIS). The principal analysis for comparing the active treatment to placebo will be performed when 117 cases of breast cancer have been diagnosed in the prevention stratum (see section 6.3 for more details). It is anticipated that this will occur after a median follow-up of 5 years. Primary endpoint data will be collected from participating women until the end of trial definition (LPLT + 5 years of follow up).

Adherence to treatment protocol will cease if a woman develops breast cancer and a breast cancer CRF should be returned. All breast cancer pathology must be reviewed by a pathologist approved by the UK National Breast Screening Programme or foreign equivalent. In addition, a tissue block or where unavailable 20 sections. will be required in consenting women for all breast tumours developing after entry into the trial.

It is recognised that breast cancer mortality is an important exploratory endpoint and this will also be analysed. However, the power to detect this within 10 years is marginal. Continued long-term follow-up beyond 10 years, as well as an overview of other similar trials will be needed to obtain clear results on this question. Total and cause-specific mortality will be analysed and the Final CRF (if still on active treatment) and Death CRF should be returned for any woman who dies of any cause while on therapy.

All women will be followed up for cancer incidence (breast and other cancers) and cause of death using available NHS registries as described in section 4.5.1.4. During the 5-year period of active follow-up and the post-treatment follow-up period serious medical conditions will be recorded including myocardial infarction and other heart problems, thromboembolic events (superficial and deep), cardiovascular events, osteoporosis, fractures, and other cancers.

Basic information on prescriptions and hospital visits during the 5 years of active treatment for each participant will also be recorded.

### **6.3 Numbers of Volunteers and Power**

The sample size for the prevention stratum will be a minimum of 3500 (although target will be 4000 to allow for possible changes in subsequent patient characteristics).

**Three factors determine the numbers needed for this study. They are (i) the absolute risk level of the participants, (ii) the size of the smallest reduction thought to be worthwhile and (iii) compliance rates.** Initially assumptions were based on an incidence of 6 cases of breast cancer per 1,000 women per year for high-risk women (as in IBIS-I), and a compliance adjusted breast cancer reduction of 50% for anastrozole. However interim figures indicate that incidence is much higher. The overall event rate is 6.6 cases of breast cancer per 1000 women per year which, with a 50% reduction in the anastrozole arm, would translate to 9 cases of breast cancer per 1000 women per year for placebo. Thus the expected number of new cancers in each arm after 5 years of median

follow-up for a total trial size of 3,500 is 78 for placebo and 39 for anastrozole leading to an expected chi square of 13 and power in excess of 90% for a 5% significance level.

### **Long term follow-up Volunteers and Power**

Participants from three participating countries will be included in the long-term follow up study, based on good data return during the active clinical trial, number of endpoints, and number of participants recruited. For a 60% reduction with anastrozole compared to placebo, 2584 participants and 208 events over the next 10 years would be needed to achieve a power of 90% ( $\alpha=0.05$ ) (superiority).

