### **3.2 Dose and Duration**

Women will be randomised in a 2-arm design to receive one of the following:

1. Anastrozole 1mg
2. Anastrozole placebo

Randomisation will be stratified by major (hub) centre. Randomised blocks will be used to maintain balance. Randomisation will be performed centrally by electronic contact with the main trial centres in the UK and will be available at all times. All treatment will be on a daily basis for 5 years. Tablets will be supplied in numbered, light-proof containers containing a 6-month supply. Each container will have extra tablets to allow for some delay in the next appointment. See Appendix 2 for further details of drug handling procedures.

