#### **4.5.1.3 Post- treatment Follow-up Questionnaires (PTQ) - beyond 10 years**

The 16 year follow-up results from the IBIS-I Trial (Cuzick et al, 2015) was seminal in determining the long-term benefits of tamoxifen as prophylaxis for breast cancer. This confirmed that “the risk-reducing effect of tamoxifen appears to persist for at least 10 years, but most side effects of tamoxifen do not continue after the 5-year treatment period”. Collection of breast cancer occurrence for extended follow up periods (beyond 5 years) will be pivotal in determining if the effect of anastrozole, like tamoxifen, can persist for at least 10 years.

The ATAC trial 10 year follow-up results (Cuzick et al., 2010) extended the previously reported superior efficacy of anastrozole over tamoxifen. Furthermore, results demonstrated a carryover benefit for recurrence in the hormone-receptor positive population, which is larger than that previously shown for tamoxifen. This highlights the need for continued long term follow-up in IBIS-II, collecting breast cancer occurrence data up until the end of trial definition in 2022. Published results from this trial (Cuzick *et al.* 2014) have already been published at median average follow up of 5 years (IQR 3·0–7·1), 40 women in the anastrozole group (2%) and 85 in the placebo group (4%) had developed breast cancer (hazard ratio 0·47, 95% CI 0·32–0·68,  $p < 0·0001$ ). Sustained

follow up is required to see if this difference persists and in the case of similar tamoxifen trials, may further diverge.

Sites should continue to follow-up those participants that have reached 10 years of follow-up beyond this time in the same way as for years 6 – 10 (section 4.5.1.2). Data will be collected on events of interest to meet primary and secondary endpoints as described in section 6.2.

Participants have been contacted by their trial site to seek their consent for follow-up beyond 10 years. This should be collected at the last PTQ visit at the year 10 post-treatment visit. Consent will be documented via completion of an electronic CRF at the trial site and can be done verbally on the phone or by paper CRF if the site posts the questionnaires for completion. The post-10-year phase of the IBIS-II trial should be considered as an additional observational element to the trial. Key safety data will nevertheless be collected as described before and reviewed as part of final study analysis, and forwarded to AstraZeneca.

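### The long-term follow-up power statement in section 6.3 is internally inconsistent: a 60% reduction at 90% power needs about 51–58 events, not 208

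*Protocol*

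**What the plan says.** The long-term part of Protocol section 6.3 (Long term follow-up Volunteers and Power) restricts this phase to three countries and sizes it in one sentence. The effect and the requirement are given together: "For a 60% reduction with anastrozole compared to placebo, 2584 participants and 208 events over the next 10 years would be needed". The purpose is "to achieve a power of 90" per cent, with alpha 0.05 and a superiority hypothesis. The sentence does not give the sidedness, formula, placebo risk or allocation ratio. It also mentions no allowance for loss to follow-up or dilution of the effect.

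The main calculation in section 6.3 assumes a 50% reduction, with 78 cases expected on placebo and 39 on anastrozole, "leading to an expected chi square of 13 and power in excess of 90" per cent at the 5% level.

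On allocation, section 3.2 says "Women will be randomised in a 2-arm design to receive one of the following", and adds "Randomised blocks will be used to maintain balance". No ratio is given, but 78 against 39 at a 50% reduction implies equal arms.

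**The concern.** At a fixed alpha and power, a larger effect needs fewer events. Section 6.3 runs the other way: 117 events give more than 90% power for a 50% reduction, yet 208 are said to be needed for only 90% power at a 60% reduction. This ordering is wrong whichever standard formula is used.

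At stake is what the long-term phase is understood to detect. This sentence is its only numerical justification. A reader who takes it at face value would think that 208 events are barely enough for a 60% reduction and that anything smaller is out of reach. In fact 208 events have good power for considerably smaller effects. That matters when a long-term result weaker than 60% has to be interpreted.

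**Working it through.** **Inputs.** Hazard ratio (HR) 0.40 (60% reduction), power 90%, alpha 0.05 and superiority come from the long-term part of section 6.3. Two arms come from section 3.2. Equal allocation and a two-sided test are assumptions; one-sided results are also shown.

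**Step 1. The main calculation reproduces.** (78 − 39)² / 117 = 13.0. Power is Φ(√13.0 − 1.960) = Φ(1.646), about 95%, or 96% by Schoenfeld. This agrees with the protocol's claim of more than 90%.

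**Step 2. Events for the stated long-term inputs.** (1.960 + 1.282)² = 10.507.

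- Schoenfeld: 4 × 10.507 / (ln 0.40)² = 42.03 / 0.8396 = 50.06, so 51 events.
- Freedman: (1.40 / 0.60)² × 10.507 = 57.2, so 58 events.
- One-sided: 41 and 47 events.

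The stated 208 is 208/58 = 3.6 to 208/51 = 4.1 times the two-sided requirement.

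**Step 3. What 208 events deliver.**

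- Power at HR 0.40: Schoenfeld Φ(½ × √208 × 0.916 − 1.960) = Φ(4.65); Freedman Φ(√208 × 0.60/1.40 − 1.960) = Φ(4.22). Both exceed 99.99%.
- HR detectable at 90% power: Schoenfeld exp(−√(42.03/208)) = 0.638; Freedman 0.633. This is a reduction of about 36–37%.

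**Step 4. Could an unstated adjustment explain 208?**

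- Loss of events: 1 − 58/208 = 72% to 1 − 51/208 = 75% would have to be lost.
- Unequal allocation: about 6:94 would be needed (Schoenfeld).
- Stricter alpha: even 0.0001 needs only 128 (Schoenfeld) or 146 (Freedman).
- Two proportions: 208 events in 2584 women at a 60% reduction means 11.5% against 4.6%. That needs 650 participants for 90% power (708 with continuity correction), not 2584.

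**Step 5. Which inputs do return 208?**

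| HR | Power | Schoenfeld | Freedman |
|---|---|---|---|
| 0.40 | 90% | 51 | 58 |
| 0.50 | 95% | 109 | 117 |
| 0.60 | 90% | 162 | 169 |
| 0.60 | 95% | 200 | 208 |

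With (1.960 + 1.645)² = 12.995, Freedman at HR 0.60 and 95% power gives (1.60/0.40)² × 12.995 = 207.9. The same formula at HR 0.50 and 95% power gives 9 × 12.995 = 117.0, the event count of the principal analysis.

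For participants, assume a 10-year placebo risk of 10%. Then N = 208 / [1 − (0.90 + 0.90^0.6)/2] = 2580. Rounding the anastrozole event-free proportion to 0.939 gives 2584.

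The protocol's own placebo rate of 9 per 1000 per year fits less well. The 10-year risks are 1 − exp(−0.09) = 8.6% and, at HR 0.60, 1 − exp(−0.054) = 5.3%, so N = 208/0.0693, about 3000.

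**The case against.** The strongest reply is that the calculation does not show which figure is wrong. It shows only that effect, power and event count cannot all be right together. That stands. A reader might infer that the sponsor certainly meant HR 0.60 and 95% power, but the documents do not say so. Correcting only the effect to HR 0.60 gives 162–169 events at the stated 90% power, so a second slip has to be assumed. The match to 2584 needs a placebo risk that the protocol does not state, and its own rate gives about 3000. The fit is close, but it is an inference.

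Other stronger readings also fail:

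- **The follow-up is underpowered.** It is not, for a 60% reduction: 208 events are far more than enough.
- **The sentence is the only justification for extended follow-up.** Section 4.5.1.3 gives a scientific rationale, namely the persistence of benefit in an earlier tamoxifen prevention trial and carryover in an adjuvant anastrozole trial.
- **The final analysis has a wrong event target.** Nothing is triggered by 208. Section 6.2 ties the principal analysis to 117 cases, and section 6.6 ties the end of trial to the last patient's last visit.
- **A 60% reduction is implausibly optimistic.** It exceeds the 53% seen at the first analysis, but HR 0.40 lies inside the reported interval ("hazard ratio 0·47, 95% CI 0·32–0·68").

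The reply does not rescue the sentence. No adjustment stated in section 6.3 closes a fourfold gap, and the conflict with the 117-event calculation does not depend on how 208 arose.

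**Conclusion.** The concern holds as an internal inconsistency in a stated power calculation. The event count is 3.6 to 4.1 times what the stated effect, power and alpha require, assuming equal allocation and a two-sided test; a one-sided test widens the gap. A misprint of HR 0.60 as a 60% reduction, with 95% power written as 90%, is a plausible origin, but it remains for the sponsor to confirm. The consequence is limited to what the document tells its reader about the detectable effect. Neither the conduct nor the adequacy of the follow-up for a 60% reduction is called into question.

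**What to change.** Correct the sentence in section 6.3 so that effect, power, events and participants agree. State the hazard ratio, the sidedness of alpha, the formula and the assumed 10-year placebo risk. The sponsor should go back to the calculation behind 208 and 2584 and choose accordingly:

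- If HR 0.60 (a 40% reduction) was intended, say so, and state that 208 events give about 95% power (Freedman) to 96% (Schoenfeld). About 162–169 events would suffice for 90%.
- If a 60% reduction at 90% power was intended, restate the events needed as about 51–58 and recompute the participants.
- If neither was intended, state the inputs that were used, including any allowance for loss or dilution.

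The cost is one corrected sentence and a check of the sponsor's calculation records. Conduct does not change.
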